### Statistical methods

#### The number of DVA cases detected per team

We will use Generalized Estimating Equations analysis to compare detection rate in the intervention and control teams. Independent variables will be number of detections each CMH team over 12 month follow-up period. The number of patients in each CMH team will be included as denominator, and CMH team will be included as a random effect to take the clustered nature of the data into account. Subsequent analysis will be adjusted for the number of detected cases at baseline. Sensitivity analyses will be conducted to evaluate the impact of team characteristics (such as case load size, proportion of clinicians trained on DVA, and proportion of female patients) on the intervention outcomes. Due to the nature of our study, we will not have any missing data.

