### Sample size

With regards to our primary research aim, we will test the hypothesis that the intervention condition will result in a significantly higher rate of detected cases of DVA compared to the control condition over a 12 month follow up period.

To calculate the sample size needed in this cluster RCT, we started with a sample size calculation assuming individual randomization and inflated this number by a design effect to account for randomization by cluster [36]. This inflation factor (IF) is dependent on average cluster size, and the intra-class correlation (ICC). Using this calculation we found that with a minimum of 12 intervention teams and 12 control teams, with the assumption of a detection rate of 0.25% in control teams (based on the LARA study [13]) and an ICC of 0.03 (based the IRIS study [30]) we will be able to detect a three- to four-fold increase (Beta = 3.55) in the detection rate with a power of 80% and a significance level of 0.05. This calculation assumes an average of 200 patients in every team.

Regarding knowledge and attitudes on DVA, a sample size of 24 teams allows us to detect a large sized increase of knowledge between the intervention and control teams.

In order to answer Aim 2 we will ask a purposeful sample of persons from every profession involved in the study for an in depth interview about the feasibility, sustainability and acceptance of the intervention. A minimum of ten interviewees will be selected from the DVA services, and ten from CMH services. Furthermore all trainers in this study will be interviewed on their experiences. Additionally, we will interview a total of 30 patients or more until saturation of the themes is achieved.

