#### Survey on knowledge and attitudes on DVA

Subscale scores from BRAVE survey will be calculated. For each participant change scores will be calculated between baseline and follow-up score. Generalized Estimating Equations analysis will be used to compare mean change score in the intervention and control teams. The CMH team will be included as a random effect to account for the clustering of the data. Questionnaires with more than 5% of the questions missing will be removed from the sample. Questionnaires with less than 5% missing will be imputed using multiple imputation.

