## Discussion

DVA is a problem worldwide and particularly vulnerable groups, such as psychiatric patients with severe mental illness, become victims of DVA while at the same time DVA often remains undetected in this group by mental health professionals. In this protocol, we will measure the efficacy of an intervention to improve knowledge and skill training for professionals about DVA and mental illness, as well as to implement a referral pathway between CMH and DVA services for DVA victims with mental illness. According to these premises, we underline the importance of this intervention for psychiatric patients suffering from DVA.

This study is the first cluster randomized controlled trial targeting both male and female psychiatric patients who potentially experience DVA, using an intervention that involves a training of mental health and DVA services, and the focus on the implementation of a referral protocol. Among victims of DVA, loss to follow up is considered a risk. MacMillan et al. [34] reported 42% loss over an 18 months follow up period. This high percentage loss is partly due to the nature of the problem studied. Victims of DVA show a high level of mobility and might be at high risk for subsequent violence after disclosure of the DV. By assessing our primary outcomes at team level, we minimize biases caused by individual drop out.

Furthermore, by randomizing teams we avoid contamination of skills and techniques of professionals in the intervention condition to the professionals in the control condition. However, since a cluster RCT is less precise than an individual trail, the chance of failing to detect a true intervention effect might increase (type II error). Also, the number of clusters in this trail is relatively small (i.e. 24 clusters), therefore randomization might partly fail, which would cause the patients in the control and intervention condition to differ from each other [39].

We do not foresee many risks in the attainment of this study. However, possible risks could occur if the mental health institutions discontinue facilitation of the CMH teams or reorganize the team structure, for instance by merging existing teams during the study period. This will affect the number, size and composition of clusters. This might lead to contamination and decrease of power. Also, municipal reorganization of the DVA services might affect the attainment of this study.

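### The primary analysis is written as a GEE with team as a random effect and detections as an independent variable: two different models, with different false-positive rates on 24 teams

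*Protocol article*

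**What the plan says.** The protocol article, *Statistical methods – The number of DVA cases detected per team*, opens: "We will use Generalized Estimating Equations analysis to compare detection rate in the intervention and control teams". It then says: "Independent variables will be number of detections each CMH team over 12 month follow-up period". Team size is handled as follows: "The number of patients in each CMH team will be included as denominator". For clustering, the same sentence of the article goes on to state: "CMH team will be included as a random effect to take the clustered nature of the data into account". Baseline enters in a further step: "Subsequent analysis will be adjusted for the number of detected cases at baseline".

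The next subsection, *Survey on knowledge and attitudes on DVA*, also names GEE and repeats the clustering term: "The CMH team will be included as a random effect to account for the clustering of the data".

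*Sample size* sets the number of clusters ("with a minimum of 12 intervention teams and 12 control teams"), the ICC (0.03), the control detection rate (0.25%) and the significance level (0.05, sidedness not given). The *Discussion* concedes that "the number of clusters in this trail is relatively small (i.e. 24 clusters". It raises the risk of chance imbalance there and, one sentence before, loss of precision and type II error. It does not mention false positives.

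**The concern.** A GEE handles clustering through a working correlation and a robust (sandwich) variance, and it contains no random effects. A mixed model handles clustering through an estimated variance component. The article asks for both at once, so the primary model cannot be fitted as written. Detections are the primary outcome under *Primary outcome*, so they belong on the left-hand side. Arm, the real exposure, is not named as a model term.

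The primary outcome is one rate per team, and *Ethics* says the primary data are collected at team level. Analysed as one count per team, the data contain no within-team correlation to estimate. A GEE then rests wholly on the sandwich variance across 24 teams, which is biased downward when clusters are few. A random-effect model rests on something else. An analyst who settles the question after seeing the data would be choosing between p-values for the confirmatory test.

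**Working it through.** The article gives no achieved type I error, only the nominal 0.05, so there is no figure of its own to reproduce. The check asks how far the candidate readings differ.

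**Inputs from the protocol article:** 12 + 12 teams, ICC 0.03, control rate 0.25% and alpha 0.05 (*Sample size*); 200–250 patients per team (*Study design*).

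**Assumptions not in the article:** two-sided test; team size uniform on 200–250; beta-binomial variation between teams; control rates above 0.25%; ICCs other than 0.03.

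**Data under the null.** Team rate ~ Beta(p·k, (1−p)·k) with k = 1/0.03 − 1 = 32.3. Team count y ~ Binomial(m, team rate), with the same p in both arms.

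**Reading A, log-link GEE with offset log m.** With arm as the only term:
- estimate: ln(Y₁/M₁) − ln(Y₀/M₀), where Y and M are arm totals of detections and patients;
- uncorrected sandwich variance: sum over the two arms of Σ(y − μ)²/Y², where μ = m·Y/M;
- Mancl-DeRouen correction: divide each residual y − μ by 1 − m/M, and refer to t on 24 − 2 = 22 df.

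**Reading B, team random effect.** Poisson-gamma count model by maximum likelihood, with Wald z and likelihood-ratio tests.

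Rejection at nominal 5%, ICC 0.03 (20,000 trials per row for A, 1,500 for B):

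| Control rate | A: uncorrected, z | A: Mancl-DeRouen, t(22) | B: Wald | B: likelihood ratio |
|---|---|---|---|---|
| 0.25% | 11.8% | 6.1% | 3.8% | 2.5% |
| 1% | 12.8% | 8.2% | 7.1% | 5.1% |
| 2.5% | 9.7% | 5.8% | 6.9% | 5.7% |
| 5% | 8.0% | 4.6% | 7.9% | 6.5% |
| 10% | 8.2% | 4.9% | 6.5% | 5.3% |

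Monte Carlo standard errors are about 0.2–0.3 points for A and 0.5–0.7 points for B. A repeat simulation of reading A gave 7.6–12.6% uncorrected and 4.3–8.1% corrected.

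**Sparse data.** At 0.25% an arm expects only 12 × 225 × 0.0025 = 6.75 detections. About 25% of null trials had an arm with none, and the first row excludes them. Counted as non-rejections, 11.8% becomes 0.118 × 0.7495 = 8.8%.

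**Sensitivity.** Over ICC 0.005–0.05 and the same rates, the uncorrected z test runs at about 7–16%.

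**Price of the correction.** With equal teams, m/M = 1/12, so the standard error grows by 12/11 = 1.091. The critical value grows from 1.960 to 2.074, a factor of 1.058. Intervals on the log scale are about 1.091 × 1.058 = 1.15 times as wide.

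**The case against.** The strongest reply is that this is a condensed article whose analysis plan is not shown. It names no variance estimator, reference distribution or degrees of freedom, and these are commonly left to that plan. A reader might infer that the trial has no small-sample correction and that its primary test runs at 8–13%. The article does not support that, because it neither plans nor excludes a correction. This part of the objection stands.

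It is also true that the random-effect reading, taken literally, stays near nominal, so inflation belongs to one reading only. With a log link and a random intercept unrelated to arm, both readings target the same rate ratio. The dispute is then about standard errors and p-values.

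Three further inferences should be resisted:
- that clustering might be ignored altogether: the text says it will be taken into account;
- that the survey test is shown to be inflated: it was not computed, and individual change scores give several respondents per team, so the one-count-per-team argument does not carry over;
- that the *Discussion* identifies this problem and leaves it untreated: its remark on few clusters concerns imbalance, which stratification and the planned adjusted and sensitivity analyses partly address.

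Calling detections independent variables is, alone, probably a slip, since *Primary outcome* makes the outcome clear. None of this removes the contradiction. The article does state a model for the primary comparison and states it inconsistently, and the same clustering term recurs in the survey analysis.

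**Conclusion.** The contradiction is certain: GEE and a team random effect are different models, and the outcome is listed on the wrong side. It affects the primary analysis and, in wording, the survey analysis.

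Its size is conditional. If the model is fitted as a GEE with an uncorrected sandwich and z test on 24 teams, the nominal two-sided 5% test would run at about 8–13% at ICC 0.03. A random-effect count model would run at about 4–8% (Wald) or 2.5–6.5% (likelihood ratio). A GEE with Mancl-DeRouen and t(22) would run at about 5–8%. These figures rest on beta-binomial team variation and control rates of 0.25–10%. At the protocol's own 0.25%, they also exclude the quarter of null trials with an empty arm. The choice should be settled before outcome data are analysed.

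**What to change.** State one model in *The number of DVA cases detected per team*. If GEE is kept, for example:

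> The dependent variable is the number of patients with detected DVA per team over 12 months. A log-link Poisson GEE will be fitted with arm as exposure, log number of patients as offset and team as the cluster; there is no random effect. Standard errors will use the Mancl-DeRouen corrected sandwich, with a t reference on the number of clusters minus the number of parameters. If data are sparse or an arm has no detections, the p-value will come from a permutation test within the randomisation strata.

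The draft should say what counts as sparse. A fallback is needed because the corrected test still ran at 8.2% at a 1% rate and the log rate ratio is not estimable with an empty arm. The permutation should also respect the blocks of 2. If these form 12 complete pairs, there are 2¹² = 4,096 allocations, ample for a 5% test.

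Alternatively, drop GEE and name a mixed count model with team as random effect, together with its test and the same fallback. Either route is defensible. The offset should stay the number of patients, as the article states.

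Reconcile the survey subsection in the same way: either GEE with team as cluster, or a mixed model with team as random effect.

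The cost is protocol or analysis-plan wording, a few lines of code and, under the corrected GEE, intervals about 15% wider on the log scale than with the uncorrected default.

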### Eligibility criteria for CMH teams

Subjects (teams) which meet any of the following criteria will be excluded from participation in this study:Teams providing care to patients <18 yearsTeams with more than 20% of the employees working over different teamsTeams specialized in one specific mental illness (e.g. autism)Teams without a functioning electronic patient file system or with <12 months of historical data at the start of the intervention.

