### Randomization and blinding

We will randomly allocate the 24 CMH teams in a 1:1 allocation ratio to receive either no intervention or the BRAVE intervention. Randomization will be conducted using a web-based computer-generated randomization schedule ten-ALEA (randomization software programme, version 2.2), using block sizes of 2. Social-economic status of the service area of the CMH team dichotomized into high and low social-economic status, will be used as stratification factor. Allocation will be facilitated by an independent researcher. Due to the nature of this intervention, it is not possible to blind the CMH professionals of the teams for allocation status. An independent researcher, blinded for allocation, will be responsible for extracting the primary data fields regarding the primary outcome measure (e.g. the number of screened DVA cases per team) from the electronic patient files.

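### The main comparison of detection rates names neither the SES stratum nor baseline detection; including both costs little, but the gain is conditional and may be nil at the stated 0.25% control rate

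*Protocol article*

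**What the plan says.** All points are in the protocol article.

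- *Randomization and blinding*: "We will randomly allocate the 24 CMH teams in a 1:1 allocation ratio to receive either no intervention or the BRAVE intervention". Allocation is made "using block sizes of 2", with SES of the service area "dichotomized into high and low social-economic status, will be used as stratification factor".
- *Eligibility criteria for CMH teams*: a team is excluded if it has no working electronic file system or has "<12 months of historical data at the start of the intervention". Every randomised team therefore has a year of files from which a baseline rate can be taken.
- *The number of DVA cases detected per team*: the main analysis is a GEE comparison of detection rates by arm, with the number of patients as denominator and team as the clustering unit. No other term is named. The next step is: "Subsequent analysis will be adjusted for the number of detected cases at baseline". Sensitivity analyses then look at team characteristics "such as case load size, proportion of clinicians trained on DVA, and proportion of female patients".
- *Discussion*: the number of clusters is relatively small, "therefore randomization might partly fail".

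**The concern.** With 24 teams, differences between teams dominate the error, and a team's own earlier detection rate is the obvious covariate to explain them. The plan makes that history a condition of entry and already intends to count baseline cases, yet keeps them out of the leading comparison. SES is used to balance the arms but is not named in the model. Blocks of two within SES strata hold SES close to balance, so a model that ignores SES leaves the variation due to SES in the error term and tends to overstate the standard error.

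At stake are precision, which is scarce with 12 teams per arm, and protection against chance imbalance in baseline detection. There is also a wording risk in the sensitivity list. If the proportion of clinicians trained were measured after allocation, it would be close to the arm indicator itself.

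**Working it through.** **Inputs from *Sample size*.** Control rate 0.25%, ratio 3.55, ICC 0.03, 200 patients per team, 12 teams per arm. *Study design* gives caseloads of about 200–250. The article gives no year-to-year correlation of team rates and no SES effect, so both are assumptions below.

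**The plan's own figure.** The article states no precision figure for adjustment, only 80% power overall. The design effect is 1 + 199 × 0.03 = 6.97, so the effective number per arm is 2400/6.97 = 344. A two-sided comparison of 0.25% with 0.8875% (3.55 × 0.25%) at that size has power of about 0.20, not 0.80. That is a separate problem. It matters here only because it makes recoverable precision more valuable.

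**Variance removed by baseline.**
- Reliability of a team's observed rate: m × ICC / (1 + (m − 1) × ICC) = 200 × 0.03/6.97 = 0.861.
- Correlation of observed baseline and follow-up rates: r = 0.861 × ρ, where ρ is the assumed correlation of true team rates.
- Variance factor after adjustment: 1 − r². Equivalent unadjusted teams per arm: 12/(1 − r²).

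| ρ (assumed) | r | variance factor | variance cut | equivalent teams per arm |
|---|---|---|---|---|
| 0.3 | 0.258 | 0.933 | 7% | 12.9 |
| 0.5 | 0.430 | 0.815 | 19% | 14.7 |
| 0.7 | 0.603 | 0.637 | 36% | 18.8 |
| 0.8 | 0.689 | 0.526 | 47% | 22.8 |

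**Dependence on the ICC.** At ICC 0.001 the reliability is 0.2/1.199 = 0.167 and the factor is 0.97–0.99 for ρ between 1 and 0.5. At ICC 0.005 it is 0.75–0.94. A low ICC is a live possibility. Taken together, 0.03 and 0.25% imply a between-team coefficient of variation of √(0.03 × 0.9975/0.0025) = 3.46, which is very large.

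**SES.** If SES explains a share s of between-team variance, the factor is 1 − 0.861 × s. Assumed shares of 5% to 30% give 0.96 to 0.74. The documents support no particular value.

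**Baseline information at the stated rate.** 200 × 0.0025 = 0.5 cases per team. In simulation, 74% to 84% of teams had no baseline case, depending on the assumed form of the team effects.

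**Simulated power.** Arm alone was compared with arm + SES + log((baseline cases + 0.5)/patients), using a corrected sandwich variance and a t reference. ICC is 0.03. The SES rate ratio of 1.5, the values of ρ and the control rates of 1.5%, 5% and 10% with their ratios are assumptions. Only the 0.25% and 3.55 rows use the article's figures.

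| control rate | ratio | ρ | arm only | adjusted |
|---|---|---|---|---|
| 10% | 1.6 | 0.7 | 50% | 70% |
| 5% | 2.0 | 0.7 | 59% | 74% |
| 5% | 2.0 | 0.3 | 59% | 62% |
| 1.5% | 2.0 | 0.7 | 30% | 36% |
| 0.25% (stated) | 3.55 | 0.7 | 37% | 32% (milder correction) |
| 0.25% (stated) | 3.55 | 0.7 | 32% | 19% (stronger correction) |

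The choice of correction also matters at 5%. With ρ = 0.3, the stronger (Mancl–DeRouen) correction gives 56% against 54%, so the small gain is lost. A team-level t-test on log rates shows the same pattern: 60% against 75% at 5%, and 24% against 25% at 0.25%, both with ρ = 0.7. The variance formula alone would predict a rise at 0.25% from 0.20 to 0.285 at ρ = 0.7, but it does not allow for how poorly a log rate built on half a case behaves.

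**The case against.** The strongest reply has five parts.

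- **The unadjusted comparison is valid.** Ignoring a stratification factor is usually conservative, not biased. This stands: the issue is efficiency and fit to the design, not validity.
- **SES may be covered elsewhere.** A reader might infer that no analysis includes SES. The text does not support that. The list of team characteristics is open, and a fuller protocol or SAP may name SES. What can be said is that the article describes its main comparison without it.
- **Baseline adjustment is already planned, and in a stated order.** A reader might infer two competing results with no order between them. The article does give one: the GEE comparison first, the adjusted analysis after. What remains is that the better-suited model is placed second.
- **Using a count instead of a rate is harmless here.** It is tempting to add that a raw baseline count wastes precision. With 200–250 patients per team, count and rate correlate at 0.994–0.998 and the variance factor moves by at most about 0.004. A rate is tidier, nothing more.
- **The trained-clinicians covariate may be measured at baseline.** Section 2 of the BRAVE survey asks about previous courses, and the survey is given at baseline, so a harmless reading exists. It is also only a sensitivity analysis and cannot remove the primary effect. What stands is that the time of measurement is not stated.

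**Conclusion.** The point holds as a conditional improvement to the leading model. The plan stratifies by SES and requires a year of history, yet describes a main comparison that uses neither.

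At ICC 0.03 and 200 patients per team, baseline adjustment would cut team-level variance by 7% to 47% for assumed year-to-year correlations of 0.3 to 0.8. If the ICC is near 0.001 there is almost nothing to gain. A reader might infer from the larger figures that the plan discards substantial precision. The documents do not support that as a general statement. It needs stable team rates and a control rate well above 0.25%, and the article gives neither. At its own 0.25%, the log-baseline-rate model showed no power gain and in some runs a loss.

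The case for change therefore rests on agreement with the stratified design, on guarding against the imbalance the article itself expects, and on a possible gain in precision from data already to be collected.

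**What to change.** - **Primary model.** Prespecify one: arm, SES stratum, and baseline detection rate obtained with the same file search as the outcome, with a named small-sample correction. Report the unadjusted comparison as supportive.
- **Fallback.** State in advance that the model reduces to arm plus SES if baseline cases are too sparse, for example if more than half of the 24 teams have none. Make that decision on baseline data only, before any follow-up outcome is seen.
- **Sensitivity analysis.** Define the proportion of clinicians trained as the baseline share of staff reporting a previous DVA course (BRAVE survey, section 2). Do not use attendance at the trial's own training.

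**Cost.** The change is to analysis wording, because the baseline count is already planned. Two degrees of freedom are spent: with 24 teams, residual degrees of freedom fall from 22 (intercept and arm) to 20. If detection is as rare as 0.25%, the return on that cost is little or nothing, which is why the fallback must be fixed beforehand.
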